### Methods for additional analyses (e.g., subgroup analyses) {20b}

In an exploratory way, we will perform exploratory correlational analyses between the changes observed on our measures with the changes observed in 18F-DOPA influx to analyze the relationship between the neural and psychological mechanisms of change.

### Methods in analysis to handle protocol non-adherence and any statistical methods to handle missing data {20c}

Using an intent-to-treat analysis strategy allows to include all participants having completed the pre-test measures in case of drop-outs. In case of drop-outs, last observations will be carried forward.

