### Relevant concomitant care permitted or prohibited during the trial {11d}

FM participants will be withdrawn from the study if they receive treatment with medication affecting the central DA system, including opioids, neuroleptics, antileptics, antidepressive, and lithium, or if they have to undergo an examination with radiopharmaceutical or radioactive marked substances or if they begin another regular psychotherapeutic treatment or participate in another clinical trial during the course of the study until completion of the post-test measures. All other treatments are allowed during the course of the study. For healthy participants participating in PET measures at pre-test, the same conditions are applicable until the end of pre-test measures. For healthy participants not participating in the PET measures, the same conditions are applicable with exception of the examination with radiopharmaceutical or radioactive marked substance. Concomitant treatment will be recorded at each study visit in the eCRF.

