### Participant timeline {13}

The overall study duration is 4 years from June 2021 to June 2025. Recruitment will take place during the entire study duration as we will perform 4 successive groups of the MORE intervention. The study duration per participant will be between 6 and 8 months, depending on scanner availability for the pre- and post-test measures. As soon as we have a minimum of 10 FM participants (minimum 5 participants and maximum 10 participants per MORE group), we will start with the first MORE group. The first measures will ideally be performed on healthy participants. The FM participants will be randomized after screening, and the ones assigned to the MORE intervention will undergo the pre-test measures of FM first. We plan 4 to 5 weeks to perform the pre-test measures for the participants allocated to the MORE group (2 participants per week). The first MORE will take place in the center where we will have first recruited the necessary number of participants. During the duration of the first MORE group (8 weeks), we will make the pre-test measures for the non-intervention control group and begin the pre-test measures for the second MORE group. This will allow us to begin with the second group as quickly as possible after the completion of the first group. During the second MORE group, we will perform the post-test measures for the first MORE group participants and test the non-intervention controls of the second MORE group. During fall 2021, we will test participants of the healthy control group and recruit the participants for the next two MORE groups that will take place in winter/spring 2022, according to a similar schedule for the first 2 groups. In parallel, we will perform the follow-up measures for MORE 1 and MORE 2. FM participants allocated to the non-intervention group will have the possibility to participate in a MORE group at the earliest after all participants of the group have completed follow-up measures, i.e., around 20 weeks after pre-test-measures (8 weeks delay for post-test measures + 12 weeks after post-test measures). In the years 2023 and 2024, we will complete the measures for the control group as well as the follow-up measures for the FM groups.

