
Another barrier of recruitment is going to be the requirement of randomization into immediate or delayed groups. As such, participants will have to make themselves available for program dates over a period of 5 months, in case they are randomized to the waitlist groups. Logistically managing simultaneous baseline and follow-up measures can be challenging. Another issue is drop-outs or missing data. By using an online format for the questionnaires, we aim to eliminate incomplete datasets. Due to the forced-answer format of the questions in the questionnaires, no missing data is to be expected. In case of missing data, the last observation will be carried forward. Drop-outs will be replaced in order to reach the targeted number of complete participants in the study. To evaluate the influence of drop-outs, analyses will be first performed with complete datasets only and compared to results of intent-to-treat analyses where all participants are included. Lastly, most clinical outcomes are patient-reported and related to pain, which are heavily influenced by knowledge of assigned intervention so this could possibly influence the outcomes.

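### Last observation carried forward enters a zero pre/post change for anyone lost before post-test, and the primary analysis set is not fixed

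*Protocol article*

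**What the plan says.** Section {20c} gives the rule for drop-outs: "In case of drop-outs, last observations will be carried forward". The Discussion repeats it for missing data in general: "In case of missing data, the last observation will be carried forward".

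The main analysis (Planned analyses {20a}) is a group × time ANOVA with two levels of time, pre-test and post-test. A third level is added only for follow-up analyses. The trial design section, Table 2 and the PET acquisition section place PET at T1 and T2 only, and T3 consists of questionnaires. The abstract also lists PET at 3 months, which the methods do not support.

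On the analysis set, {20c} says: "Using an intent-to-treat analysis strategy allows to include all participants having completed the pre-test measures in case of drop-outs". The participant timeline {13} says: "The FM participants will be randomized after screening", and {16a} confirms that randomisation comes before the pre-test.

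The Discussion adds two further rules. One is replacement: "Drop-outs will be replaced in order to reach the targeted number of complete participants in the study". The other is the order of analyses: "analyses will be first performed with complete datasets only and compared to results of intent-to-treat analyses where all participants are included". Neither analysis is called primary.

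The sample size section takes 20 per fibromyalgia group as the minimum, inflates to 25 for 20% drop-out, and rounds up to 32 for technical data loss and MORE group size.

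**The concern.** In a two-point design the last observation before post-test is the baseline. Carrying it forward asserts that every participant lost between T1 and T2 did not change at all, and does so with certainty, including for a scan that was never made. For questionnaires at T3, someone lost between T2 and T3 keeps the T2 value, which assumes that any effect lasts.

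Drop-out is expected, and it need not be equal: one arm attends eight weekly sessions, the other attends none, and nobody is blinded. Section {11d} adds protocol-driven losses: "FM participants will be withdrawn from the study if they receive treatment with medication affecting the central DA system". The only companion analysis is complete cases, which does not test whether drop-out depends on outcome.

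Two further gaps bear on the same result. If completer and intent-to-treat results differ, the plan does not say which one decides, and in an open-label trial that choice could be made after the results are known. The intent-to-treat set also leaves out people randomised but lost before the pre-test. The timeline schedules the MORE arm's pre-tests first and tests the controls later, during the course, so that loss can differ by arm.

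**Working it through.** **Inputs from the article.** Minimum 20 per arm, planned drop-out 20%, 32 per arm randomised, cited pain effect d = 0.5, and cited trial counts of 115 at start and 69 at post-intervention.

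**Assumed, not in the article.** Two-sided α = 0.05; pre/post correlation 0.6; all unequal drop-out rates; a shared change of 0.5 SD where stated; drop-out unrelated to outcome. Effects are in baseline SD units unless noted.

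**1. The plan's own figure.** 20 / (1 − 0.20) = 25, which reproduces. The cited counts give (115 − 69) / 115 = 40% lost by post-intervention measures. The article elsewhere puts drop-out in the same trial at 20%, or more than 20%.

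**2. Equal drop-out.** Let m₁ and m₀ be the mean changes among those measured, and q₁ and q₀ the drop-out fractions (1 = MORE, 0 = control). With baseline carried forward,

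difference = (1 − q₁)m₁ − (1 − q₀)m₀.

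With q₁ = q₀ = q this is (1 − q)(m₁ − m₀):
- q = 0.20: 0.80 × 0.50 = 0.40
- q = 0.40: 0.60 × 0.50 = 0.30

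With correlation 0.6 the variance of change is 2(1 − 0.6) = 0.8. The carried-forward variance in an arm is (1 − q) × 0.8 + q(1 − q)m². At 32 per arm, with m₁ = 0.5 and m₀ = 0, power is about 60% with full data, 49% at 20% drop-out and 38% at 40%. With no treatment effect, the rejection rate stays at about 5%.

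The rule also gains nothing over completers. If a 0.5 effect is expressed in SDs of change, 20% drop-out gives 41% power with carry-forward at 32 per arm, against 41–42% for 25–26 completers per arm. The completer estimate is not shrunk in this setting.

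**3. Unequal drop-out, no treatment effect, both arms change by m.** The false difference is m(q₀ − q₁). For a shared improvement, m = 0.5:

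| Drop-out, MORE vs control | False difference | Standard error | Type I error |
|---|---|---|---|
| 20% vs 5% | 0.5 × (0.05 − 0.20) = −0.075 | 0.213 | about 6–7% |
| 40% vs 20% | 0.5 × (0.20 − 0.40) = −0.10 | 0.195 | about 8% |
| 40% vs 10% | 0.5 × (0.10 − 0.40) = −0.15 | 0.200 | about 12% |

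The standard error in the last row is √[(0.6 × 0.8 + 0.4 × 0.6 × 0.25 + 0.9 × 0.8 + 0.1 × 0.9 × 0.25) / 32] = √(1.2825 / 32) = 0.200. Simulation with 100,000 replicates gave 6.5%, 8.3% and 11.9%.

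The minus sign means against MORE: in the last row, 11.6 of the 11.9 percentage points favour control. If both arms worsen by 0.5 SD, the signs reverse and the false rejections favour MORE at the same rates. Milder inputs give little inflation: 25% versus 15% gives about 5.8%, and a shared change of 0.25 SD with 40% versus 20% also gives about 5.8%.

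**4. Analysis set, by comparing sections.** {13} and {16a} place randomisation before the pre-test, while {20c} requires a completed pre-test. The set described is therefore not all randomised participants. The number affected cannot be derived from the article.

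**The case against.** At the planned 20% in both arms, carry-forward only dilutes the effect and does not inflate type I error. A completer comparison is already specified to show the influence of drop-outs. Both statements are correct, and they limit the size of the problem. They do not justify the rule, which shrinks the estimate without gaining power.

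Four stronger readings are tempting and should not be drawn.

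- A reader might infer that replacing drop-outs and running completers first undo intent-to-treat. The Discussion keeps an intent-to-treat analysis and compares the two. What is missing is which one is primary and how replacements are randomised and counted.
- A reader might infer that replacement counts the drop-out allowance twice. The article does not say whether the target number of complete participants is 20, 25 or 32, and it attributes the step from 25 to 32 to other causes. It is fair to say only that drop-out had already been allowed for.
- A reader might infer that those withdrawn under {11d} are the ones who worsened. That is plausible for some triggers, but the section lists events and says nothing about outcome.
- A reader might take a 12% type I error as false efficacy. With shared improvement and more drop-out in MORE, it is false inferiority of MORE.

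Nor does carry-forward give every drop-out a zero change: someone lost between T2 and T3 keeps the observed T2 change.

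**Conclusion.** The concern holds in limited form. For the T1–T2 comparison of Ki, VRS and BPI, the stated rule enters a zero change as data for everyone lost in between. The shrinkage with equal drop-out is arithmetic: 20% at the planned rate and 40% at the rate in the cited counts. The type I figures are illustrations that rest on the assumed correlation, shared change and unequal drop-out rates. They show that the direction of bias is not predictable, and they do not forecast its size in this trial.

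The unnamed primary analysis and the pre-test condition on the intent-to-treat set are faults of specification whose numerical effect cannot be derived from the article. Because these rules govern both main outcomes of an open-label trial, they should be settled before outcome data are compared by arm.

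**What to change.** Delete last observation carried forward in {20c} and in the Discussion. Name one primary analysis: all randomised fibromyalgia participants in their assigned arm, in a likelihood-based mixed model for repeated measures with arm-by-visit terms, using every observed value. Use T1 and T2 for PET and fMRI, and T1, T2 and T3 for questionnaires. The model cannot recover a missed scan, but it does not invent one. Report by arm how many were randomised without a pre-test.

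Keep sending the online questionnaires to participants who stop MORE or are withdrawn, unless they withdraw consent. Add one delta-adjusted or reference-based sensitivity analysis, and label the completer analysis supportive. If drop-outs are replaced, keep those who dropped out in the analysis, randomise each replacement as a new participant, and state the target number.

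The cost is wording, a different analysis procedure and some questionnaire reminders. No extra scans are needed.

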### Plans to give access to the full protocol, participant-level data, and statistical code {31c}

Full protocol, anonymous participant-level data, and statistical code are available from the corresponding author upon request.

## Oversight and monitoring

### Composition of the coordinating center and trial steering committee {5d}

The coordinating center is at the University of Fribourg and the trial steering committee is led by CMS and KL. Regular meetings are taking place between (1) the study staff involved in the recruitment, screening, and conductance of the study on a weekly basis (online meetings) and (2) all investigators

### Composition of the data monitoring committee, its role, and reporting structure {21a}

Monitoring visits at the investigator’s site prior to the start and during the course of the study will help to follow up the progress of the clinical study, to assure the utmost accuracy of the data, and to detect possible errors at an early time point. The sponsor organizes professional independent monitoring for the study. All original data including all patient files, progress notes, and copies of laboratory and medical test results will be available for monitoring. The monitor will review all or a part of the eCRFs and written informed consents. The accuracy of the data will be verified by reviewing the above referenced documents. The investigator’s site will collaborate with the Appletree CI group.

### Adverse event reporting and harms {22}

During the entire duration of the study, all serious and non-serious adverse events (SAEs) that may be causally related to the study intervention are collected and documented in source documents. Reportable events are recorded in the case report form (CRF). Study duration encompassed the time from when the participant signs the informed consent until the last protocol-specific procedure has been completed including a safety follow-up period of 12 weeks (see follow-up measures). The recording of serious and non-serious adverse event (SAE and AE) information includes the time of onset, duration, resolution, action to be taken, assessment of intensity, and relationship with study treatment. Participants will be asked about health problems, mood worsening, and negative thoughts as well as any emergency medical or hospitalization that could have happened between 2 study visits at each visit, beginning at pre-test. Participants who prematurely stop the study will be asked for adverse events at the time, when they stop at the end of the study visit.

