## Assignment of interventions: blinding

### Who will be blinded {17a}

Because there is no active control group or no placebo intervention in this study, the study staff and the participants will be unblinded.

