### Safety analysis

Safety analysis includes the report and observation of potential side-effects of the MORE intervention. Should side-effects occur, we will analyze the characteristics of the participants concerned.

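### Adverse event collection is limited to events possibly related to the intervention, which conflicts with the open questioning in the same section and, if followed, prevents comparing clinical events by randomised arm

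*Protocol article*

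**What the plan says.** The collection rule is the opening sentence of Adverse event reporting and harms {22}: "all serious and non-serious adverse events (SAEs) that may be causally related to the study intervention are collected". The next sentence sends reportable events to the case report form.

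The rest of that section is broader:
- The observation period opens at informed consent and includes a 12-week safety follow-up.
- "Participants will be asked about health problems, mood worsening, and negative thoughts as well as any emergency medical or hospitalization" since the previous visit. This is done at each visit, starting at pre-test, with no limit by arm or cause.
- The details kept for each event include "assessment of intensity, and relationship with study treatment".

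Three other places bear on the rule:
- Intervention description {11a}: control women receive no intervention and continue usual treatment.
- Who will be blinded {17a}: "the study staff and the participants will be unblinded".
- Safety analysis: "Safety analysis includes the report and observation of potential side-effects of the MORE intervention". If side-effects occur, the characteristics of the women affected are examined. No comparison of arms is stated.

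**The concern.** The opening sentence makes possible causality a condition of entry into the safety data, for serious events as well as others. Causality is normally an attribute recorded after an event has been collected.

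Fibromyalgia has a fluctuating course, so some women in both arms can be expected to have mood worsening, emergency care or hospital admission for reasons unrelated to MORE. Randomisation separates that background from any harm of MORE, but only if events are counted the same way in both arms. A rule that admits events by their presumed link to an intervention that one arm does not receive cannot do this. Too little attribution in the MORE arm would look like safety, and too much would look like harm. The Discussion of the article itself accepts that knowledge of assignment can influence patient-reported outcomes.

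The article hopes that its findings will inform care providers about using MORE, so the safety record matters beyond this trial.

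**Working it through.** The article gives no adverse event rate and no safety sample size, so there is no figure to reproduce. The check sets the provisions side by side and follows the rule through each arm.

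**Step 1: what the rule requires.** The term study intervention can be read in two ways: (a) MORE only, or (b) MORE plus the PET scan, MR scan and reward task, which Table 2 lists under Interventions and which both FM arms undergo.

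| Kind of event | MORE arm | Control arm |
|---|---|---|
| Possibly due to MORE | Collected | Cannot arise |
| Possibly due to scans or task | Collected under (b) only | Collected under (b) only |
| Judged unrelated to either | Not required | Not required |

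Under both readings, the last row, which is the background, is outside the rule in both arms.

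**Step 2: what a comparison of collected events would estimate.** Per woman, let
- *b* = mean number of background events, equal in the two arms in expectation by randomisation;
- *m* = mean number of extra events caused by MORE;
- *s* = mean number of collected scan-related events, assumed equal in the arms (zero under reading a);
- *a* = proportion of MORE-caused events that are judged possibly related;
- *f* = proportion of background events in the MORE arm that are judged possibly related to MORE.

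Under the stated rule:
- MORE arm: *a·m + f·b + s*
- Control arm: *s*
- Difference: *a·m + f·b*

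Under recording regardless of cause, with all scan-related events counted in *s*:
- MORE arm: *m + b + s*
- Control arm: *b + s*
- Difference: *m*

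The two differences agree in general only if *a* = 1 and *f* = 0, that is, if attribution is perfect. Any study staff member who judges causality does so knowing the arm. The control arm supplies no estimate of *b*, so the error cannot be corrected afterwards from the collected events.

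**Step 3: whether the section agrees with itself.** Three provisions fit poorly with the opening sentence:
1. Observation starts at consent and questioning at pre-test, before any MORE session, when no event can be due to MORE.
2. The questions cover health problems, mood, negative thoughts, emergencies and admissions without reference to cause or arm.
3. Relatedness is recorded for each event. It could still grade events already thought possibly related, but it does its full work only if unrelated events are present too.

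No sentence says that events judged unrelated are kept, so these provisions do not lift the restriction. They show that the section points in two directions.

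**Step 4: what is still compared by arm.** Table 1 schedules the BDI, POMS, BPI, VRS and FIQ-R at T1, T2 and T3 in both FM arms. The Statistical methods analyse the pain scores and the clinical outcomes by treatment group × time. Average deterioration in mood, pain or function under MORE would therefore be visible. Discrete clinical events, such as emergency care and hospital admission, would not be.

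**The case against.** The strongest reply is that the section already asks everyone about everything at each visit and records relatedness, so the opening sentence may simply be loosely worded and all events may in practice be kept. This stands in part. A reader might infer that the trial obtains information and then discards it, including unrelated serious events. The document does not say so, and that should not be claimed. It also does not say that such events are kept. If they are, the opening sentence is wrong; if they are not, the comparison is lost. The text needs changing either way.

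Other replies also narrow the point:
- A reader might infer that the control arm has no collectable events at all. That is true only of MORE-related events. Given the listing in Table 2, scan-related events in controls may be collected, so the document does not support a claim that PET-related events go unrecorded. Scan-related events give no comparison for MORE.
- A reader might infer that harms of MORE cannot be compared in any form. The questionnaires contradict this for average mood and pain.
- The section does not name who judges causality. The unblinding statement covers study staff as a whole, so judgement with the arm known is likely but is an inference.
- The definition of a reportable event and the layout of safety tables can be left to the full protocol or analysis plan, and the Safety analysis wording does not exclude a table by arm. That is fair. But an analysis plan cannot tabulate events that the collection rule never required, and that rule is stated here.
- With 32 women per arm, a comparison of events would be imprecise. It would indeed be descriptive, which limits the gain but does not justify a rule that differs in effect between arms.

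**Conclusion.** The point holds in a limited form. The opening sentence of the harms section restricts collection to events possibly related to the study intervention, and it conflicts with the unrestricted questioning and the relatedness field in the same section. If the sentence is followed, clinical adverse events and serious adverse events cannot be compared by randomised arm, because background events need not be collected in either arm and MORE-related events cannot arise in controls.

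No numerical size can be attached from the documents. The effect is that a difference in collected events estimates *a·m + f·b* instead of *m*, with *a*, *f* and *b* unknown. This rests on the rule being applied literally and on causality being judged with knowledge of the arm. Efficacy analyses are unaffected, and average mood and pain worsening remains comparable. The change should be made, but the flaw does not undermine the trial's main results.

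**What to change.** Reword the opening sentence of Adverse event reporting and harms {22} so that every serious and non-serious adverse event elicited at study visits is recorded in both FM arms, whatever its presumed cause. Keep relatedness as an attribute of each event, as already planned, and state whether it refers to MORE, to the scans, or to each separately. In Safety analysis, add a descriptive table of all events by randomised arm, with related events as a subset. Base that table on the visits common to both arms, because the weekly MORE sessions give that arm more contact with staff.

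The cost is more eCRF entry. The questions are already asked at each visit, so no extra visit, instrument or assessor is needed. For women already seen, events can be added only where their answers were kept in source documents, and the trial report should state which rule was actually applied. If only related events were kept, they should be reported without a between-arm safety claim.

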### Intervention description {11a}

FM participants will participate in the MORE intervention or in a non-intervention control group. The non-intervention control group does not include any intervention. The MORE treatment is manual-based [28], consists of 8 sessions, and offers instruction in applying mindfulness and related skills to the following topics: discriminating between nociception, pain, and suffering; gaining awareness of automaticity and coping habits in chronic pain; disrupting the link between negative emotions, catastrophizing, and pain experience through reappraisal; refocusing attention from pain and life stressors to savor pleasant experiences; promoting acceptance instead of suppression of experience; and developing a mindful recovery plan. Mindfulness training will involve mindful breathing and body scan techniques, with an emphasis on developing metacognitive awareness and shifting attention from affective to sensory processing of pain and craving sensations. Sessions will be audio recorded for control of therapists’ adherence with the manual. MORE participants will be asked to engage in daily 15-min mindfulness practice sessions at home guided by a MP3 recording of the meditations. MORE is a manualized intervention that is centered on three therapeutic processes: mindfulness, reappraisal, and savoring. The MORE manual and the meditations are translated in French and in German. The non-intervention control group includes continuation of treatment as usual.

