**Interventions**					
***F-DOPA PET scan***			**x**	**X**	
***MR scan***			**X**	**X**	
***Reward task***			**X**	**X**	

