#### PET data acquisition

PET images will be acquired at the Department of Nuclear Medicine at the University Hospital Zurich. MRI overlay images will be acquired at 3 Tesla at the Department of Nuclear Medicine at the University Hospital Zurich, using T1-weighted sequence (MP-RAGE) to provide an anatomical framework for image analysis. 18F-DOPA is a well-validated measure of presynaptic DA function [45], and previous studies showed differences in 18F-DOPA binding between FM and healthy participants at rest [74, 75]. Subjects will have an intravenous catheter placed in their forearms. One hour before scanning, they will receive as routinely an oral dose of carbidopa 100 mg, a peripheral DOPA decarboxylase blocker and entacopone 400 mg, a peripheral catechol O-methyltransferase antagonist, and an additional 50 mg dose of carbidopa 30 min before 18F-DOPA injection in order to provide increased availability of 18F-DOPA for striatal uptake. The purpose of the premedication regimen is to limit the metabolism of the 18F-DOPA tracer by peripheral enzymes, i.e., DOPA decarboxylase and catechol O-methyltransferase, thereby maximizing central uptake [54]. Subjects will lay quietly before administration of the tracer to allow them to habituate into the environment and to relax. Subjects will then be injected with approximately 100 MBq of 18F-DOPA. Dynamic scanning will be performed up to 100 min after injection of tracer, but at least between 40 and 90 min after injection (cite https://www.ncbi.nlm.nih.gov/pmc/articles/PMC5584692/). Scans will be acquired on a PET/CT Discovery 690 scanner. Subjects will undergo the PET and MRI measures on the same day at the same place. Participants will have time to rest and to have lunch between both measures. PET measures will take place at pre-test and post-test. Pre-test measures take place 6 weeks to 1 day before the beginning of the MORE intervention. Post-test measures take place from 1 day after completion of the MORE intervention (i.e., + 8 weeks and 1 day after the beginning of the MORE intervention) to 6 weeks after completion of the MORE intervention (i.e., + 14 weeks after the beginning of the MORE intervention).

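### Adverse events are kept only if they may be related to the study intervention, a judgement made knowing the arm, so the control arm gives no comparable background count

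*Protocol article*

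**What the plan says.** The collection rule is in Adverse event reporting and harms {22}: "all serious and non-serious adverse events (SAEs) that may be causally related to the study intervention are collected and documented in source documents". The condition acts on source documents, before the further step in which reportable events go to the CRF.

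The same section contains four provisions that help the plan:
- Participants are asked about their general health, mood, negative thinking and any emergency care or admission "that could have happened between 2 study visits at each visit, beginning at pre-test". No group is exempt.
- "Participants who prematurely stop the study will be asked for adverse events at the time" that they stop.
- The 12-week follow-up is designated as safety follow-up.
- Each recorded event carries an assessment of intensity and of relationship to study treatment.

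Three other sections bear on the rule:
- Safety analysis: "Safety analysis includes the report and observation of potential side-effects of the MORE intervention".
- Intervention description {11a}: "The non-intervention control group does not include any intervention". Usual treatment continues.
- Who will be blinded {17a}: "the study staff and the participants will be unblinded".

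**The concern.** A randomised control arm is the natural source of a background rate for harms. In fibromyalgia, low mood, more pain and unplanned care are expected without any course. A count of such events in the MORE arm means little unless the same kind of event is counted in the same way among controls.

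The stated rule makes retention depend on possible causation by the intervention. That question has a ready answer for a woman attending MORE and almost none for a woman receiving nothing. The person answering it on the study staff knows which woman is which. An event left out of the source documents is lost for good, so no later choice of analysis can repair this.

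**Working it through.** The protocol gives no adverse event rate and no safety sample size, so there is no figure of its own to reproduce. The check is mainly of the text.

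**Step 1: what can be kept in each arm.** The term study intervention is not defined in the article, so take both plausible readings.
- *It means MORE*, as in Safety analysis. Controls are offered MORE only after the follow-up assessment, so up to T3 no control event can logically qualify.
- *It also covers the procedures listed under Interventions in Table 2*, which include the "F-DOPA PET scan". A control event then qualifies if it may be due to a scan. In the MORE arm an event qualifies if it may be due to a scan or to the course. Low mood halfway through the eight weeks could be kept in the MORE arm and has no route to being kept in the control arm.

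The counts are not comparable on either reading.

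**Step 2: where the loss arises.** Questioning at visits is the same for all, and women who stop early are asked. The loss therefore arises when answers are filtered. If every event were meant to be kept, the opening condition would be wrong. If only possibly related events are kept, the common questioning of controls is largely wasted.

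**Step 3: direction, as an illustration only.** Suppose MORE is harmless. Let b be the true share of women with an event, the same in both arms, and let aM and aC be the shares of those events judged possibly related in the MORE and control arms. The apparent excess among kept events is b × (aM − aC). All inputs are assumed: b of 10, 20 or 40%, aM of 25, 50 or 75%, aC of 0, 10 or 25%.
- Lowest: aM = aC = 25% gives 0 points.
- Middle: 0.20 × (0.50 − 0.10) = 0.08, or 8 points. In women this is 32 × 0.20 × 0.50 = 3.2 against 32 × 0.20 × 0.10 = 0.64.
- Highest: 0.40 × (0.75 − 0) = 0.30, or 30 points.

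Keeping all events removes this term, provided that women in both arms report equally.

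**Step 4: what a full count could show.** With 32 per arm and assumed counts, Newcombe 95% intervals are:
- 6/32 against 6/32: 0 points (−19 to 19).
- 13/32 against 6/32: 22 points (about −1 to 42).

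Even complete recording supports description only.

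**The case against.** The strongest reply is that the effect is small in practice. The phrase may be sets a low threshold, questioning is the same in all groups, and relationship is a recorded field. Worsening pain and mood are also measured in both arms at T1 to T3 by the BPI, BDI, POMS and FIQ-R. The protocol plans no between-arm test of adverse events. All of this stands and limits the weight of the point. It does not remove the stated retention rule, and the scales do not capture discrete events such as an admission.

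Three stronger readings are tempting, and the documents do not support them.
- *A reader might infer that PET events go uncollected.* The PET preparation involves trial-only drugs ("they will receive as routinely an oral dose of carbidopa 100 mg", with a further dose and entacapone), and Safety analysis names only MORE. However, Table 2 lists the scan under Interventions, and the full protocol or its operating procedures would commonly settle the term. This is a wording clarification.
- *A reader might infer that the 20 healthy women among the 84 scanned (24%) have no contact after the scan.* They have T1 only, and no later visit is stated. But PET and MRI share a day in an unstated order, and ambulatory sampling may fall in the week after PET. The 24% is not established.
- *A reader might infer that the follow-up carries no safety enquiry because it is done by online questionnaire.* The harms section designates it as safety follow-up.

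**Conclusion.** The point holds for the collection rule and for reporting limited to side-effects of MORE. It rests on stated text: the relatedness condition at source level, open allocation, and a control arm with nothing to attribute events to. It assumes that sites apply the rule as written.

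Its numerical size is unknown. The 0 to 30 points above reflect assumed inputs and do not estimate bias in any planned result. Neither the primary nor the secondary efficacy analyses are touched. The change is worth making because the information is already being elicited and cannot be recovered later.

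**What to change.** **Adverse event reporting and harms {22}.** Delete the relatedness condition. Record all adverse events elicited at T1, T2, the T3 safety follow-up and early stop, in all groups, whatever the judged cause. Keep relatedness as a field, assessed separately for MORE and for PET with its premedication. Add a sentence naming PET and premedication as covered for every scanned woman, including the healthy women, for whom no later visit is stated.

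**Safety analysis.** Report the recorded events descriptively by group, in place of side-effects of MORE alone. Base any comparison of the two fibromyalgia arms on the contacts they share, because MORE participants also attend eight weekly sessions and controls attend none.

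**Cost.** Two edited paragraphs and somewhat more CRF entry. Reporting stays unblinded, contact stays unequal and arms of 32 stay small, so the tables should carry no formal inference.
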